## Abstract

Tongue diagnosis is an important procedure in traditional Korean medicine (TKM). In particular, tongue coating thickness (TCT) is deemed to show the progression of the disease. However, conventional tongue diagnosis has limitations because of various external factors. Therefore, it is necessary to investigate the availability of tongue diagnosis system (TDS) in the assessment of TCT. This study has been designed as a prospective clinical trial involving 60 patients with functional dyspepsia. Tongue images will be obtained by TDS twice with a 30 min interval. The system will measure the percentage of TCT and classify it as either no coating, thin coating, or thick coating according to the existing diagnostic criteria. After finishing the collection of 60 patients' tongue images, TCT on the images will be simultaneously evaluated by the conventional method to establish the gold standard for assessing TCT by 5 well-trained clinicians. The evaluation will be repeated by the same clinicians after 2 weeks, but the order of the images will be changed. This trial is expected to provide clinical evidence for the availability of TDS as a diagnostic tool and to contribute to the standardization of the diagnosis system used in TKM. This trial is registered with ClinicalTrials.gov NCT01864837.

## 1. Introduction

Tongue diagnosis is an important diagnostic procedure that is used in traditional Korean medicine (TKM) to examine the physiological function and pathological changes of the internal organs. It involves the examination of the body of the tongue (its color, shape, moisture, and movement) and the coating on the tongue (its color, thickness, distribution, and characteristics at the root) [1, 2]. The coating is believed to reflect the condition of the stomach as well as the nature and the site of the pathogenic factors. In particular, tongue-coating thickness (TCT) is considered to reflect the progression of a pathological condition [3]. A conventional method used in tongue diagnosis involves direct examination of a protruded tongue by a practitioner, so the result is not only affected by his or her subjectivity but also by environmental factors such as light [4]. Moreover, the available diagnostic criteria are insufficient and vague. 

To overcome the above limitations, a number of tongue diagnosis systems (TDSs) have been developed in recent years [5]. In general, TDS has a number of components including image capturing and storage, color correction, tongue segmentation, and image analysis. The processes of image capturing and storage are hardware resources, while those of color correction and tongue segmentation are image-preprocessing steps in tongue diagnosis. In the process of image analysis, the tongue is classified according to selected diagnostic parameters [5, 6]. In this study, tongues will be classified based on the measurement of TCT into those with no coating, thin coating, or thick coating according to the criteria developed by Kim et al. [7].

Functional dyspepsia (FD) is chronic or recurrent dyspepsia without evidence of organic disease [8]. The prevalence of FD is from 11.5% to 14.7% in the general population in Western countries [9], while in Republic of Korea, 25% of the population is affected as shown by a recent epidemiological survey [10]. We decided to include patients with FD in our study, because according to TKM, FD is one of the common stomach diseases that are well reflected by various features of tongue coating [11, 12]. 

For the objective and standardized tongue diagnosis system in TKM, it is necessary not only to develop an objective diagnostic tool but also to propose a new study protocol for clinical trial. We aimed to investigate the agreement between the results provided by TDS and those obtained by the conventional method in the assessment of TCT, which constitutes a part of tongue diagnosis in TKM, for evaluating on the availability of TDS in practice.

## 2. Materials and Methods

### 2.1. Study Setting and Participants

This study has been designed as a prospective clinical trial on the availability of TDS as a new diagnostic tool. Because there are no data available in the literature that would indicate the effective sample size to investigate the availability of TDS, we estimated the approximate sample size based on the number of outpatients with FD presenting at the Korean Medicine Hospital of the Kyung Hee University in Seoul, Korea. 

The study will include a total of 60 patients aged 20 years and older who meet the Rome III criteria for FD [8]. Patients complaining of dyspepsia within the previous 3 months and reporting the onset of symptoms at least 6 months prior to enrollment will be included in the study. They should have 1 or more of the following symptoms: bothersome postprandial fullness, early satiation, and epigastric pain and burning, without evidence of structural disease (on upper endoscopic examination) that could explain the symptoms. 

The exclusion criteria are as follows: pregnancy, mental disorders, severe systemic organ diseases such as cancer, infectious or other serious consumptive diseases, and geographic tongue. Patients unable to open their mouths or protrude their tongues; those unable to read, write, hear, or see; and those unable to sign a written informed consent form will also be excluded.

The study will be conducted in accordance with the standards of the International Committee on Harmonization of Good Clinical Practice and the revised version of the Declaration of Helsinki. The protocol of the trial has been approved by the institutional review board of the Korean Medicine Hospital of the Kyung Hee University (IRB no. KOMCIRB-2013-01). A written informed consent will be obtained from all patients before enrollment.

All patients will be required to visit the hospital twice during the study period. At the first visit, the written informed consent will be obtained, and patients will be screened for eligibility criteria. All eligible patients will be then instructed to avoid mouth rinsing as well as food and liquid intake for 4 hours before the examination with the TDS at the next visit. 

Tongue images will be obtained with the TDS under constant conditions at the second visit. Then, the percentage of tongue coating will be measured using a TDS analysis software, and TCT will be classified with the existing diagnostic criteria [7]. To assess the reproducibility of the TDS, the images will be taken again by the same method after 30 min. After two examinations of TDS, the weight of the tongue coating (mg) will be measured quantitatively to determine the correlation with the percentage of tongue coating. 

After we complete the collection of 60 patients' tongue images, the images will be simultaneously evaluated by 5 clinicians with 5 years or more of clinical experience to establish the gold standard for the assessment of TCT. The evaluation will be repeated after 2 weeks to analyze intra- and interrater reliability of the clinicians. Finally, we will evaluate the agreement between the results provided by TDS and those obtained by clinicians. The flow of the trial is shown in Figure 1.

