### 2.5. Measurement of TDS

Patients press their face against the interface of the TDS, open their mouth wide, and protrude their tongue for a second. An operator who is well trained in the use of TDS makes sure that the patient's tongue does not bend or lean to one side by watching the tongue image on the monitor and takes a picture of the tongue when ready. TDS allows to measure tongue coating percentage and classify TCT into 1 of 3 categories—no coating, thin coating, or thick coating—according to the diagnostic criteria developed by Kim et al. [7]. They developed differential criteria for TCT and specifically proposed a standard for the assessment of thin and thick coatings in tongue diagnosis. In their study, 24 clinicians who were well trained and highly reliable participated in the assessment of TCT from 50 tongue images obtained by TDS, which measured the percentages of tongue coating. From an analysis of a proportional odds model, they suggested a cutoff point of 29.06% to differentiate between no coating and thin coating and a cutoff of 63.51% to differentiate between thin coating and thick coating. It takes about 5 minutes from positioning his or her tongue to obtaining the diagnosis result by TDS for each patient.

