### 2.6. Evaluation of System Performance

To assess the reproducibility of TDS, tongue images will be taken twice with a 30 min interval. Considering inevitable variations in length, angle, and shape of the protruding tongue in taking images, it will be necessary to have an appropriate interval between the two examinations to more accurately investigate the reproducibility of TDS. A 30 min interval will be able to prevent patients from intentionally protruding their tongues as they had done in the first examination. Then, we will compare TCT as shown on two different images for each patient.

After two examinations of TDS, we will measure the weight of the tongue coating with a method described by Yaegaki and Sanada [13] to analyze the correlation between the real quantity of tongue coating and the percentage of coating measured with TDS. The coating will be collected from each patient by the following procedure: first, cotton rolls will be put around the tongue to remove moisture; then, saliva on the dorsal surface of the tongue will be removed with a stream of air and pure pulp tissue paper; finally, the coating will be carefully collected with a tongue scraper from the terminal sulcus to the apex of the tongue; and the tongue dorsal surface will be cleaned with cotton pellets immersed in physiological saline. The weight of the coating will be then measured with a microbalance.

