### 2.8. Establishment of Gold Standard

To establish the gold standard for the assessment of TCT, 5 clinicians with 5 or more years of clinical experience and working at the Korean Medicine Hospital of the Kyung Hee University will be included in the trial to assess the images obtained by TDS. Before participation in the study, they will augment their knowledge about conventional methods of TCT assessment and be well trained in TCT differential criteria to obtain a reliable gold standard. The images will be sequentially presented to the clinicians using a picture-viewer software and an LCD monitor (DN-50PZ66, 50′′ HD, 1366 × 768 resolution, LG, Korea). Each image will be displayed for 10 seconds (10 minutes in total). Clinicians will be expected to label each image as either “no coating,” “thin coating,” or “thick coating.” Their assessment will be considered as a gold standard, and if there is a disagreement, we will choose the majority as the final diagnosis. All assessments will be performed individually in the same room and under the same conditions (in terms of brightness and distance between the clinician and the monitor). Clinicians will be blinded to the assessment of other clinicians and clinical data of the patients. The assessment will be repeated after 2 weeks and will involve the same clinicians, but the images will be presented in a changed order. The comparison of the 2 assessments will allow us to analyze the intra- and interrater reliability of the clinicians.

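### The TDS percentage is available before the coating is scraped and weighed, with no stated masking of the person who scrapes: an avoidable risk to the secondary percentage-weight correlation

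*Protocol article*

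**What the plan says.** Section 2.1 of the protocol article gives the sequence at the second visit. A first image is taken and analysed: "Then, the percentage of tongue coating will be measured using a TDS analysis software, and TCT will be classified with the existing diagnostic criteria". Imaging is repeated by the same method after 30 minutes. The weight comes last: "After two examinations of TDS, the weight of the tongue coating (mg) will be measured quantitatively to determine the correlation".

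Section 2.5 gives the turnaround of the device: "It takes about 5 minutes from positioning his or her tongue to obtaining the diagnosis result by TDS for each patient". Section 2.6 confirms the interval ("To assess the reproducibility of TDS, tongue images will be taken twice with a 30 min interval") and describes the collection. The tongue is dried with cotton rolls, an air stream and tissue paper; then "the coating will be carefully collected with a tongue scraper from the terminal sulcus to the apex of the tongue"; the material is weighed on a microbalance.

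Section 2.2.2 lists the percentage-weight correlation as a secondary outcome, and section 2.9 assigns it Pearson's coefficient. Section 2.8 contains the only blinding statement, which concerns the image readers: "Clinicians will be blinded to the assessment of other clinicians and clinical data of the patients". The article does not say who scrapes and weighs, or whether that person is the TDS operator.

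**The concern.** The weight is the only planned comparison of the TDS with a physical quantity. The primary kappa compares the device with clinicians' labels, the reproducibility analysis compares it with itself, and its cutoffs (section 2.5) were derived from clinicians' ratings. The value of the correlation therefore rests on the weight being obtained independently of the percentage.

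The microbalance reading is objective, but the amount that reaches the balance depends on how dry the tongue is made and how firmly and completely it is scraped. If someone who knows a high percentage scrapes more thoroughly, the error in the weight becomes positively associated with the TDS value. Pearson's r would then be too high, in favour of the device.

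**Working it through.** **Timing, from the article.** The first result takes about 5 minutes (2.5) and the second examination follows at 30 minutes (2.1, 2.6). That leaves 30 − 5 = 25 minutes between the first percentage and the second image. Scraping comes later still.

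**Does any step before weighing need the percentage?** Tongue position is judged on the monitor image before the picture is taken (2.5). The percentage is calculated afterwards from the captured image, once the operator has marked the boundary (2.4). The clinicians read the images only after all 60 patients' images have been collected (2.1). No described step at the visit uses the percentage.

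**Size of a possible bias.** The article gives no expected correlation, so there is no figure of its own to reproduce. The following is an illustration. Inputs from the article are n = 60 (2.1) and a significance level of 0.05 (2.9), taken here as two-sided. Everything else is assumed.

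With standardised percentage P and weight W, let the recorded weight be W + bP, where b is the shift in SDs of weight per SD of percentage. Then

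observed r = (r + b) / √(1 + b² + 2br).

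If the coefficient of variation of weight is 50%, a shift of 5% or 10% of mean weight per SD of percentage gives b = 0.05/0.50 = 0.1 or 0.10/0.50 = 0.2.

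| True r | b = 0 | b = 0.1 | b = 0.2 |
|---|---|---|---|
| 0 | 0 | 0.10 | 0.20 |
| 0.30 | 0.30 | 0.39 | 0.46 |
| 0.50 | 0.50 | 0.57 | 0.63 |

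For example, with r = 0.50 and b = 0.2: 0.70/√(1 + 0.04 + 0.20) = 0.70/1.114 = 0.63.

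Varying the assumed coefficient of variation at true r = 0.50, with shifts of 5% and 10%: a value of 40% gives 0.59 and 0.65, and a value of 70% gives 0.55 and 0.60.

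**False-positive rate at true r = 0.** The critical |r| at n = 60 is 0.254. By Fisher's z with standard error 1/√57, the chance of P < 0.05 is about 12% at b = 0.1 and 32% at b = 0.2, against 5% at b = 0. A simulation of 20,000 trials gave 11.6% and 33.1%.

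**What masking could recover.** Split b into a part due to seeing the tongue and a part due to knowing the number. Masking removes only the second. If, as an assumption, half of b = 0.2 came from sight alone, masking would bring a true 0.50 from 0.63 down to 0.57, not to 0.50.

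**The case against.** The strongest objection is that nothing in the article says the scraper sees the percentage. Who scrapes, and what that person may see, is procedural detail that a journal article commonly leaves to the full protocol, which is not shown. This stands in part. A reader might infer that the weights are unblinded and the correlation is therefore inflated, and the article does not support that. What it does print is a sequence that makes the value available early without any described use for it, and that sequence can be changed.

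A reader might also infer that weighing after imaging is itself the mistake. It is not: scraping destroys what is to be photographed.

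Other objections also carry weight:

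- The scraper sees how much of the tongue is coated, which is close to what the percentage measures, so expectation exists without the number. The modelled shifts therefore overstate what masking alone would gain.
- The size and direction of the shift are assumed, and a true r of 0 between coated area and coating weight is an extreme case.
- Collection follows a cited method with moisture control and a stated extent. That method may fix further details that cannot be checked here.
- The article's time words are loose. Section 2.2.1 has the clinicians assess the images at the same time as the TDS, whereas 2.1 places their reading after all images are collected. Even so, 2.1 and 2.5 read naturally as a result produced at the visit.
- Running the device as in practice, with an immediate result, has some merit given the study's aim. Withholding the output from the scraper keeps that merit.
- Deferring all software work could reveal an unusable image when no retake is possible. This is a real cost, and the fix has to meet it.

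**Conclusion.** The point holds as a modest one. As written, the TDS percentage and class can be known before the coating is scraped and weighed, and no masking of that step is stated. This leaves an avoidable risk to the independence of the only physical comparator.

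It is not a demonstrated bias. The inflation is unknown and may be zero. The figures of 0.57 or 0.63 for a true 0.50, and of about 12% or one third false positives for a true 0, depend on assumed shifts of 0.1 or 0.2 SD and on the scraper knowing the value. They should be read as illustrations, and not as the gain to be expected from masking.

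Only the secondary percentage-weight correlation is affected. The primary agreement between the TDS and the clinicians is not. The change is worth making because it is cheap.

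**What to change.** In sections 2.1 and 2.6, state the order at the second visit as follows:

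1. Take the first image and, 30 minutes later, the second.
2. Check that both stored images are usable, and retake if necessary, before any scraping.
3. Scrape, weigh and record the weight.
4. Only then run the percentage and classification software on the stored images. Alternatively, run it earlier but withhold its output from the person who scrapes and weighs until the weight is recorded.

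Add that this person has seen no TDS percentage or class for that patient. If the full protocol already provides for this, one sentence in the article saying so is enough.

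The images, the scraping and the planned analysis stay the same. The cost is a short delay in the TDS result, or in its release, and an explicit image-quality check before scraping, since no retake is possible afterwards. Recruitment was still under way when the article was written (section 3), so the change would apply to patients not yet examined. The number already measured under the printed order should be reported with the correlation.

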### 2.2. Outcomes

#### 2.2.1. Primary Outcome

TDS will measure the percentage of tongue coating and classify TCT as either no coating, thin coating, or thick coating according to the existing diagnostic criteria [7]. At the same time, TCT shown on the images will be assessed by clinicians. We will then evaluate the agreement between the results of the TDS and the final diagnosis established by the clinicians.

#### 2.2.2. Secondary Outcome

To evaluate the performance of TDS, we will assess its reproducibility by comparing the 2 measurements of TCT in each patient and analyze the correlation between the percentage of coating measured with the TDS and the weight of coating obtained by tongue scraping [13]. Additionally, the intra- and interrater reliability will be analyzed to ensure the validity of the results obtained by 5 clinicians in the assessment of TCT.

### 2.3. Components of TDS

The TDS consists of image acquisition system, LED illuminator, case, and analysis software. It is equipped with a vision camera (HVR-2130CPA, Hyvision System, Korea) and a mount lens (H2Z0414C-MP, Hyvision System, Korea). The camera can take color images of SXGA resolution (1280 × 1024 pixels) and automatically adjust white balance, exposure time, and gain settings. To evenly illuminate the dorsal surface of the tongue, 12 white LED lamps (*φ* 5 mm; first peak wavelength of 470 nm; second peak wavelength of 580 nm; color temperature of 6800 K) are arranged around the camera and thin double diffusion plates are placed in front of the lamps. The case is equipped with a part in contact with the face and a screw for adjusting the visual axis of the camera in order to take the tongue image at an appropriate position. The part in contact with the face ensures the proper location of the patient's nose and lower jaw and keeps the external light out of the TDS even if the facial appearance and degree of tongue protrusion change when the patient opens the jaws (Figure 2).

### 2.4. Image Analysis of TDS

An analysis software program of TDS was developed to analyze the percentage of tongue coating from the captured tongue images. To calculate the percentage of tongue coating, we first extract the tongue area from the captured tongue image. TDS generates 17 nodes on the tongue image on the monitor, and the operator moves the nodes on the boundary line of the tongue with a mouse. Then, the remaining area excluding the selected tongue area is removed. TDS converts the chromaticity coordinates of the extracted tongue image in the RGB color space to those in the CIE-Lab color space. The area of the tongue body is clearly more reddish than that of the coating. The positive a* value in the CIE-Lab color space is indicated by red/magenta, while the negative value by green. Therefore, tongue coating area is extracted from the entire tongue based on the difference in the a* value. The binarization threshold point of the a* value for the extraction was set through the tongue images acquired from the previous study [7] (Figure 3).

### 2.5. Measurement of TDS

Patients press their face against the interface of the TDS, open their mouth wide, and protrude their tongue for a second. An operator who is well trained in the use of TDS makes sure that the patient's tongue does not bend or lean to one side by watching the tongue image on the monitor and takes a picture of the tongue when ready. TDS allows to measure tongue coating percentage and classify TCT into 1 of 3 categories—no coating, thin coating, or thick coating—according to the diagnostic criteria developed by Kim et al. [7]. They developed differential criteria for TCT and specifically proposed a standard for the assessment of thin and thick coatings in tongue diagnosis. In their study, 24 clinicians who were well trained and highly reliable participated in the assessment of TCT from 50 tongue images obtained by TDS, which measured the percentages of tongue coating. From an analysis of a proportional odds model, they suggested a cutoff point of 29.06% to differentiate between no coating and thin coating and a cutoff of 63.51% to differentiate between thin coating and thick coating. It takes about 5 minutes from positioning his or her tongue to obtaining the diagnosis result by TDS for each patient.

